### Power calculation

Although we are undertaking a pilot study and thus the numbers enrolled are small, table 1 indicates the power of our primary analysis to detect a range of absolute increases in adherence (10%–30%) from a variety of baseline values (50%–90%).

**Table 1 T1:** Power calculation for the pilot study, given a sample size of 80 individuals (40 per arm), across a range of baseline levels of adherence and absolute increases in that level

Baseline adherence	Absolute increase	Power
70	30	0.98
60	30	0.88
50	30	0.82
80	20	0.86
70	20	0.61
60	20	0.49
90	10	0.54
80	10	0.24
70	10	0.18

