Based on usage of DOT within the clinic populations seen at the treatment sites (ie, individuals currently identified as needing adherence support), we estimate that around 33% of patients will be at risk of non-adherence. Taking this as a minimum (as the manualised intervention is likely to be more sensitive than current risk assessments), we would expect that at least 26 of the 80 patients recruited will be identified as requiring adherence support. This sample size allows us to measure consent to enrolment for 80 individuals, data completeness for adherence and treatment outcomes for 80 individuals, data on acceptability and feasibility of the intervention package for around 40 individuals, and data on acceptability and feasibility of adherence support for at least 26 individuals (13 receiving the manualised intervention and 13 standard care).

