#### Outcomes of the pilot

The primary outcome of the study will be level of adherence, measured as the proportion of prescribed doses taken and assessed at 6 months from the start of treatment. In addition to this primary outcome, a number of secondary outcomes will also be measured, as follows:

Proportion consenting to the study.Completeness of data for measures of adherence.Proportion of patients withdrawing during the study and the reasons why.Proportion of patients identified as needing adherence support in the intervention arm.Proportion of patients offered adherence support and accepting it in the intervention arm.Documentation of which adherence-promoting activities have been implemented among patients both in the standard of care and intervention arm, and when.Detailed treatment implementation information: for example, proportion of patients completing treatment, proportion of patients still on treatment after 9 months or at study completion (whichever is the earlier).Patterns of adherence (implementation and discontinuation).Impact of manualised intervention on maintaining adherence over the duration of treatment.Process variables: adherence-related PAPA.

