#### Administration of the manualised intervention

The patient’s case manager (usually the TB clinic nurse), plus a study research nurse, will apply the intervention in partnership with the patient to identify whether personal, sociocultural and/or systems risk factors are present that suggest likely poor adherence with treatment. If these are identified, then the relevant measures outlined in the manualised intervention that may mitigate these will be reviewed and implemented with the agreement of the participant. These will be continued throughout the course of treatment or stopped if no longer deemed to be relevant or required on reassessment.

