#### Analysis and interpretation

Where possible, univariable analyses will be undertaken to compare each outcome measure listed between study arms (intervention and control). For the primary outcome (adherence), the mean percentage value will be reported by arm (intervention and control) and histograms will be used to describe the distribution of values by study arm. Binary secondary outcomes will be reported by the proportion of individuals achieving the outcome within each arm. The need to adjust for clustering by site and clinical care provider will be assessed using the cluster summary method (a t-test) to compare the cluster means or proportions (as appropriate, between arms). An assessment of the balance in baseline characteristics between the study arms will also be conducted. If randomisation has failed to evenly distribute key characteristics (eg, age, sex, ethnicity or other factors identified as important during the scoping reviews), then the cluster means or proportions will be adjusted for these differences before applying the t-test. This two-stage approach to analysis is described by Hayes and Moulton.^31^ We recognise that adherence data may be highly skewed and thus may require compensatory analytical approaches.

The analysis of the first three of our secondary outcomes will address the feasibility of a definitive trial following a similar design to the pilot. Analysis of secondary outcomes 4–6 addresses the intervention, and complements the process evaluation (see below). Analysis of the primary outcome and final secondary outcomes around treatment adherence and completion provides initial information—given the modest sample size—concerning the effectiveness of the intervention, and may assist the sample size calculation for the definitive trial. They can also offer an alert in the unlikely event that the intervention is harmful.

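### Table 1 gives power for an unclustered yes/no comparison of individuals, not for the primary outcome (mean percentage of doses) compared across two clinics per arm

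*Protocol article*

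**What the plan says.** The Power calculation section of the protocol article states that "table 1 indicates the power of our primary analysis to detect a range of absolute increases in adherence". The title of Table 1 describes the calculation as "given a sample size of 80 individuals (40 per arm), across a range of baseline levels of adherence". The table has nine rows, with baselines from 50 to 90, increases of 10, 20 or 30, and powers from 0.18 to 0.98. It gives no SD, ICC, significance level or adherence cut-off.

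Outcomes of the pilot defines the endpoint: "The primary outcome of the study will be level of adherence, measured as the proportion of prescribed doses taken", assessed at 6 months. Under Analysis and interpretation, "the mean percentage value will be reported by arm", with histograms and a warning about skew. Only secondary outcomes are called binary there. The one test named in that section is a t-test on cluster means or proportions, within a two-stage cluster-summary approach. Study design, recruitment and eligibility fixes four clinics, two per arm, with 20 patients each.

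**The concern.** Power for a difference in mean percentage of doses depends on the between-patient SD of that percentage. Under a clinic-level test it also depends on the between-clinic variation and on having four clinic summaries, which leave 2 degrees of freedom. Table 1 appears to use none of these. Its power changes sharply with baseline for the same increase (0.54, 0.24 and 0.18 for 10 points from 90, 80 and 70), which is how a binomial calculation behaves. If so, the figures labelled as power of the primary analysis belong to a different endpoint and a different test, and a reader would take from them a wrong idea of what the pilot can show about adherence.

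**Working it through.** **Step 1. Reproduce the table.** Inputs from the document: n = 40 per arm, p1 = baseline, p2 = baseline + increase. Two-sided 5% is assumed, since no level is stated. With p̄ = (p1 + p2)/2:

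power = Φ{ [p2 − p1 − 1.96·√(2p̄(1−p̄)/n)] / √([p1(1−p1) + p2(1−p2)]/n) }

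For 50+30: p̄ = 0.65, √(2·0.65·0.35/40) = 0.1067, √((0.25 + 0.16)/40) = 0.1012. So (0.30 − 0.2090)/0.1012 = 0.90, and Φ = 0.816.

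| Row | Printed | Two-proportion z-test |
|---|---|---|
| 70+30 | 0.98 | 0.976 |
| 60+30 | 0.88 | 0.888 |
| 50+30 | 0.82 | 0.816 |
| 80+20 | 0.86 | 0.861 |
| 70+20 | 0.61 | 0.612 |
| 60+20 | 0.49 | 0.497 |
| 90+10 | 0.54 | 0.538 |
| 80+10 | 0.24 | 0.237 |
| 70+10 | 0.18 | 0.175 |

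Every row agrees within 0.01. Other binary methods miss on several rows: for 50+30 the continuity-corrected version gives 0.743 and the one-sided version 0.891, and for 90+10 Fisher's exact test gives 0.206 and the arcsine method 0.821. Read as a comparison of means with a common SD, the printed powers would need an SD that changes by row, from 21.7 points (90+10) to 46.7 points (50+30). The table is therefore an unclustered yes/no calculation.

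**Step 2. Compare the variances.** A yes/no measure with mean p has SD 100·√(p(1−p)): 50, 49, 46, 40 and 30 points at p = 0.5, 0.6, 0.7, 0.8 and 0.9. That is the largest SD any 0–100% measure with the same mean can have, reached only if every patient takes all doses or none.

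**Step 3. Stated outcome, clustering ignored.** SD is assumed (15–30 points). Two-sample t-test, 78 df, SE = SD·√(2/40). At SD 20, SE = 4.47; at SD 25, SE = 5.59.

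| SD | +10 | +20 |
|---|---|---|
| 15 | 0.84 | 1.00 |
| 20 | 0.60 | 0.99 |
| 25 | 0.42 | 0.94 |
| 30 | 0.31 | 0.84 |

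The fair comparison for +10 is with 80+10 (0.24) and 70+10 (0.18). The 90+10 row puts one arm at 100%, where the SD must be zero, so a common SD of 20–25 cannot apply to it. For the same reason the fair comparison for +20 is with 70+20 (0.61) and 60+20 (0.49).

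**Step 4. Stated outcome, clinic-level t-test.** Two clinics per arm, 20 patients per clinic, 2 df (critical value 4.30), SE² = (2·SD²/40)·(1 + 19·ICC). ICC is assumed. At ICC 0.05 the multiplier is 1.95, so SE = 6.24 at SD 20 and 7.81 at SD 25.

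| SD | ICC | +10 | +20 |
|---|---|---|---|
| 15 | 0.05 | 0.24 | 0.61 |
| 20 | 0 | 0.26 | 0.64 |
| 20 | 0.05 | 0.16 | 0.42 |
| 25 | 0.05 | 0.12 | 0.31 |
| 30 | 0.05 | 0.10 | 0.24 |

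At SD 20–25 and ICC 0.05, all four values lie below the comparable printed rows. At SD 15 with ICC 0.05, or SD 20 with ICC 0, they are about equal to or above those rows.

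**Step 5. Table 1's own binary inputs under the clinic-level test.** Here no continuous SD is assumed. At ICC 0, 70+30 falls from 0.98 to 0.59 and 50+30 from 0.82 to 0.38. At ICC 0.05 they fall to 0.38 and 0.24. Clustering therefore matters even if a binary endpoint was intended.

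**The case against.** The strongest defence is that little depends on this table. The protocol says that the pilot is not for formal hypothesis testing, justifies 80 patients by deliverability and feasibility counts, and opens the power section with a caveat about small numbers. The binomial variance is also the maximum, so on the endpoint mismatch alone the table is cautious. The loss of power in Step 4 comes from the clinic-level test, not from the binary scale, and rests on an SD and ICC that the documents do not give. All of this stands, and it limits the consequence. It does not make the label right: the article presents the figures as power of its primary analysis, and they are not.

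Several stronger readings are tempting but unsupported.

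- **Dilution.** A reader might infer that, with support going to about a third of patients, the arm-level increases are the wrong effects. The document says that "we estimate that around 33% of patients will be at risk of non-adherence", but takes this as a minimum. The manualised intervention is to be administered to all patients at each review, and the arm contrast over all 80 is the planned comparison. That unsupported patients would not change is an assumption found nowhere in the text. At most, if only 33% were supported and the rest did not change, arm gains of 20 and 30 points would need 20/0.33 = 61 and 30/0.33 = 91 points among those supported.
- **Rows ending at 100%.** Their zero variance is not a fault of the binary method, because any percentage with mean 100 has none.
- **The definitive trial.** A reader might conclude that its sample size would be built on Table 1. Analysis and interpretation ties that planning to the observed outcomes instead.

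**Conclusion.** The point holds as a mismatch between Table 1 and the analysis it claims to describe. That the table is an unclustered two-proportion calculation is established by the reproduction and needs only the conventional two-sided 5% level. The direction of the error depends on which feature is considered. The binary scale alone makes the table understate individual-level power (about 0.60–0.42 for 10 points at SD 20–25, against 0.24 and 0.18). Under the clinic-level t-test with ICC 0.05 and the same SDs, the table overstates power (about 0.16–0.12 for 10 points and 0.42–0.31 for 20). That second statement is conditional, since a smaller SD or ICC narrows or removes the gap for some rows. It also takes the clinic-summary t-test as the comparison, being the only test the article names. The correction is worth making, but it does not affect the sample size, the conduct of the pilot or the arm-level comparison.

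**What to change.** Recalculate Table 1 for a difference in mean percentage of doses, using the clinic-level test with two clinics per arm, over a stated SD range (for example 15–30 points) and a stated ICC range. For arms near 100%, use an SD that the mean allows. If a yes/no endpoint was intended, define the adherence threshold, label the table as power for that endpoint rather than for the primary analysis, and still allow for clustering. The cost is one recalculated table and a sentence or two of text. Recruitment, data collection and the target of 80 stay as they are.

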### Piloting the intervention

#### Study design, recruitment and eligibility

Once the intervention is developed, proof of concept is required within the real world. This will be undertaken using a non-blinded cluster randomised pilot study that compares the manualised intervention to the usual standard of care in four London clinics treating TB. Two clinics will be randomly allocated to the intervention and two to standard of care. In the latter, the amount of support provided to patients is based on perceived need, as identified by a nurse-led review and a needs assessment. Most patients will have supported self-administered therapy, while others will be offered DOT and/or VOT if this is felt to be appropriate. We anticipate enrolment to commence in January 2020.

All consecutive patients aged 18 or over who are about to start treatment for TB, irrespective of the site of disease, will be approached to take part in the study. We will exclude individuals who are unable to provide informed consent, those already on treatment and those who are not expected to live for the duration of the study (a minimum of 6 months from starting treatment). Within the pilot study, it is essential to capture the entire treatment period for each patient in order to assess the effectiveness of the intervention. Due to the nature of the TB patient population in the UK, patients are likely to include people at greater risk of poor adherence, such as migrants newly arrived in the UK, people whose first language is not English, people with a mental health disorder, people taking immunosuppressive therapy or known to have immunodeficiency, those with a previous history of treatment for TB, or poor adherence with anti-TB medication, and people with a current or previous history of drug or alcohol misuse.

The purpose of the pilot study was not formal hypothesis testing. Given this, a target sample size of 80 patients enrolled (20 per site) was identified for the pilot study as providing useful information that can help determine whether the intervention will be deliverable within a clinical setting. It will also guide the development of a possible larger definitive study using the intervention. The four TB clinics of interest (in East and North London) each treat in excess of 60 relevant patients per annum.

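### Table 1's power figures come from an unclustered 40 v 40 comparison of yes/no proportions, which is neither the pilot's design nor its primary outcome

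*Protocol article*

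**What the plan says.** **Design.** Under Study design, recruitment and eligibility, the pilot is a "non-blinded cluster randomised pilot study that compares the manualised intervention to the usual standard of care in four London clinics treating TB". Allocation is one to one at clinic level: "Two clinics will be randomly allocated to the intervention and two to standard of care". For recruitment, the article sets "a target sample size of 80 patients enrolled (20 per site"). The same section says that formal hypothesis testing is not the purpose, and it justifies the 80 by what can be learned about consent, data completeness, acceptability and feasibility.

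**Outcome.** The outcomes section defines the endpoint as follows: "The primary outcome of the study will be level of adherence, measured as the proportion of prescribed doses taken". The analysis section then gives its summary: "For the primary outcome (adherence), the mean percentage value will be reported by arm (intervention and control").

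**Analysis.** The same section makes adjustment for clustering conditional on an assessment, to be done "using the cluster summary method (a t-test) to compare the cluster means or proportions". If baseline characteristics are unbalanced, the cluster summaries are adjusted before the same t-test. No other between-arm test is named.

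**Power.** Under Power calculation, "table 1 indicates the power of our primary analysis to detect a range of absolute increases in adherence (10%–30"%). The caption of that table reads "Power calculation for the pilot study, given a sample size of 80 individuals (40 per arm"). No number of clusters, ICC, design effect, SD or significance level appears with the table.

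**The concern.** The power section counts 40 independent patients per arm. The design section randomises four clinics, and the analysis section compares clinic summaries. These describe different calculations. Clustering reduces the effective sample size, and a t-test on four clinic values has 2 df and a critical value of 4.30 instead of 1.96. The table also appears to treat adherence as a yes/no outcome, although the trial measures each patient's percentage of doses taken.

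Two things are at stake. A reader shown power of 0.82 to 0.98 for large effects may give too much weight to a null pilot result. The same unclustered, binary calculation may also be carried into the definitive trial, whose sample size the article says the pilot may help to set.

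**Working it through.** **Inputs from the article.** Four clinics, two per arm (k = 2), 20 patients per clinic (m = 20), and nine pairs of baseline and absolute increase, written below as baseline+increase.

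**Assumptions.** Two-sided 5% (not stated, but it reproduces the table, whereas one-sided 5% does not), no dropout, ICC from 0 to 0.10, and the SDs named in step 3.

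**Step 1: reproduce Table 1.** Pooled two-proportion z-test, n = 40 per arm, no clustering:

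power = Φ{ [d − 1.96·√(2·p̄(1−p̄)/n)] / √([p1(1−p1) + p2(1−p2)]/n) }

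For 50+30: p̄ = 0.65. The null SE is √(2 × 0.65 × 0.35/40) = 0.1067 and the alternative SE is √((0.25 + 0.16)/40) = 0.1012. Power = Φ[(0.30 − 0.2090)/0.1012] = Φ(0.90) = 0.816, against 0.82 stated. All nine rows agree within 0.01 (second and third columns below). Unpooled, continuity-corrected, arcsine, one-sided and exact versions do not match all nine.

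**Step 2: the cluster-summary t-test on the same rates.**

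Variance of the arm difference = [p1(1−p1) + p2(1−p2)]/(m·k) × [1 + (m−1)·ICC]. Degrees of freedom = 4 − 2 = 2; critical t = 4.303; power from the noncentral t with noncentrality d/SE.

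For 50+30 at ICC 0: SE = √(0.41/40) = 0.1012, noncentrality = 2.96, power 0.38. At ICC 0.05 the design effect is 1 + 19 × 0.05 = 1.95, SE = 0.1414, noncentrality = 2.12, power 0.24.

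| Baseline+increase | Stated | z-test, 40 v 40 | 2-df t, ICC 0 | ICC 0.01 | ICC 0.05 | ICC 0.10 |
|---|---|---|---|---|---|---|
| 70+30 | 0.98 | 0.976 | 0.59 | 0.53 | 0.38 | 0.29 |
| 60+30 | 0.88 | 0.888 | 0.44 | 0.39 | 0.28 | 0.21 |
| 50+30 | 0.82 | 0.816 | 0.38 | 0.34 | 0.24 | 0.18 |
| 80+20 | 0.86 | 0.861 | 0.42 | 0.37 | 0.26 | 0.20 |
| 70+20 | 0.61 | 0.612 | 0.27 | 0.24 | 0.17 | 0.13 |
| 60+20 | 0.49 | 0.497 | 0.22 | 0.19 | 0.14 | 0.11 |
| 90+10 | 0.54 | 0.538 | 0.24 | 0.21 | 0.15 | 0.12 |
| 80+10 | 0.24 | 0.237 | 0.12 | 0.11 | 0.09 | 0.08 |
| 70+10 | 0.18 | 0.175 | 0.10 | 0.09 | 0.08 | 0.07 |

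The three rows ending at 100% are rough, because the intervention clinics then have no variance at all. Beta-binomial simulation gives higher values there at ICC 0 / 0.05: 0.66 / 0.49 for 70+30, 0.51 / 0.37 for 80+20 and 0.35 / 0.22 for 90+10. At ICC 0, though, 14–21% of replicates in these rows have zero between-clinic variance and were counted as significant. For 50+30 the two methods agree (simulation 0.38 / 0.25). Every simulated value is still well below the stated one.

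A design effect alone, keeping the normal critical value, gives 0.79, 0.52 and 0.57 at ICC 0.05 for 70+30, 50+30 and 80+20.

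**Step 3: the outcome as defined, a mean percentage.** Variance of the arm difference = 2·SD²/(m·k) × [1 + 19·ICC]. For a 30-point difference:

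| Assumed SD (points) | ICC | SE | Noncentrality | Power | 4.303 × SE |
|---|---|---|---|---|---|
| 20 | 0 | 4.47 | 6.71 | 0.89 | 19 points |
| 20 | 0.05 | 6.24 | 4.80 | 0.69 | 27 points |
| 30 | 0 | 6.71 | 4.47 | 0.64 | 29 points |
| 30 | 0.05 | 9.37 | 3.20 | 0.42 | 40 points |

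The last column is the 95% CI half-width at the true SE. For 10 points with SD 20, power is 0.26 at ICC 0 and 0.16 at ICC 0.05.

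Table 1's binary model implies SD = √(p(1−p)), for example 50 points at a mean of 50% and 40 at 80%. That is the largest SD a 0–100% measure can have at that mean. The binary model therefore pulls power down while ignoring clustering pushes it up, and without an SD the net effect on the real outcome is unknown.

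**The case against.** Five points on the other side deserve weight.

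- **It is a pilot.** The article disclaims formal hypothesis testing, bases the 80 on feasibility, expects only preliminary evidence on effectiveness, and opens the power section with a caveat about small numbers. No decision or stopping rule uses Table 1. This stands, and it limits the consequence. It does not make the printed figures right.
- **The outcome is continuous.** A reader might infer from step 2 that the trial's actual power is shown to fall short in every row. The article does not support that. With a small enough SD, the cluster t-test could match or exceed some entries: a 30-point difference with SD 20 gives 0.89 at ICC 0, against 0.82 stated for 50+30. The step 2 shortfall is firm only on Table 1's own yes/no rates.
- **The planned test might be said to miss most large effects.** That is too strong at low ICC. On the simulated figures, power at ICC 0 is 0.51 for 80+20 and 0.66 for 70+30.
- **The 2 df is derived, not stated.** The clustering sentence is conditional and also mentions clustering by care provider, and the section allows other approaches for skewed data. Four clinic summaries remain the likeliest reading. An individual-level test would ignore the unit of randomisation, so it would not rescue the table.
- **Four clinics allow only six allocations, so a two-sided randomisation p-value cannot fall below 1/3.** A reader might raise this, but no randomisation test is planned, so it is no fault of this plan.

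**Conclusion.** The point holds as a mismatch between the power table and the rest of the plan. Table 1 gives the power of an individually randomised comparison of two proportions, while the pilot randomises two clinics against two, names a t-test on cluster summaries and measures a mean percentage.

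On the table's own rates, approximate power for the 2-df test is 0.10–0.59 at ICC 0 and 0.08–0.38 at ICC 0.05, against 0.18–0.98 stated. Every row falls even at ICC 0, so the direction does not depend on the assumed ICC. The size does, and it also rests on two-sided 5%, four clinic summaries, equal clinics of 20 and no dropout. For the outcome actually defined, the printed figures are unsupported, because no SD is given.

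This should be fixed but does not threaten the design. A reader might conclude that 80 patients is the wrong number; that does not follow, because the target does not rest on Table 1.

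**What to change.** Withdraw Table 1. Alternatively, replace it with power, or the expected 95% CI half-width, for the arm difference in mean percentage adherence under the planned cluster-summary t-test: two clinics of 20 per arm, 2 df, stated significance level, and stated ranges of SD and ICC (for example ICC 0–0.10). The half-width suits a pilot better, since it shows directly how little an effect estimate from four clinics can settle. Changing only the number of clinics and the ICC would leave the yes/no model in place, so the SD must be stated too.

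Add one sentence saying that a null result would not be informative about effectiveness.

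The cost is one recalculated table and a sentence of text. Recruitment, allocation, data collection and the target of 80 are unaffected.
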